Photobiomodulation (PBM) has emerged as a promising non-pharmacological intervention because of its analgesic, anti-inflammatory, and anti-edematous effects. By stimulating mitochondrial chromophores, PBM enhances adenosine triphosphate production and modulates important biological processes, including inflammation, angiogenesis, lymphangiogenesis, and the release of endogenous opioids [11–13]. Although the body of evidence supporting PBM for pain management is growing, robust randomized controlled trials evaluating its effects on postpartum perineal pain and obstetric vulvar edema remain scarce.

Accordingly, this study protocol aims to describe a randomized clinical trial designed to evaluate the efficacy of photobiomodulation in reducing perineal pain during the postpartum period (change from baseline). Secondary objectives include evaluating vulvar edema, maternal functioning, urinary incontinence, sexual function, and patient satisfaction.

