### Sample size calculation

The sample size was calculated using G*Power software (version 3.1.9.7), based on a two-tailed independent-samples Student’s *t* test for the comparison of means between two independent groups. A significance level of 5% (α = 0.05), statistical power of 80% (1 − β = 0.80), and an allocation ratio of 1:1 were assumed. Based on the findings of Alvarenga et al. ^16^. a mean perineal pain score of 4.5 (SD = 3.0) was assumed for the experimental group and 2.0 (SD = 2.2) for the sham group, resulting in an estimated effect size (Cohen’s *d*) of 0.784. The analysis indicated a minimum sample size of 54 participants, with 27 participants per group, achieving an actual statistical power of 80.75%. Considering an anticipated dropout rate of 20%, the sample size was increased to 68 participants, with 34 participants allocated to each group [14–16]. 

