### Statistical analysis

Statistical analyses will be performed using the Statistical Package for the Social Sciences (SPSS), version 20.0 (IBM Corp., Armonk, NY, USA), adopting a significance level of 5% (*p* < 0.05). Descriptive statistics will be presented as absolute and relative frequencies for categorical variables and as means, standard deviations (SD), and 95% confidence intervals (95% CI) for continuous variables.

The primary analysis of longitudinal outcomes will be performed using linear mixed-effects models. Treatment group (photobiomodulation and sham), time (T0: baseline; T1: immediately after the intervention; T2: 12 h after the intervention; T3: 40 days postpartum; and T4: 3 months postpartum), and the group × time interaction will be included as fixed effects, while participant will be included as a random effect to account for the correlation among repeated measurements within the same participant. The group × time interaction will be considered the primary parameter for determining whether changes in outcomes over time differ between the photobiomodulation and sham groups. Baseline outcome values will be included in the model when appropriate.

Model assumptions will be assessed by examining the distribution of residuals and the homogeneity of variance. If substantial deviations from model assumptions are identified, appropriate data transformations or alternative statistical approaches will be considered.

For baseline comparisons, categorical variables will be analyzed using Pearson’s chi-square test or Fisher’s exact test, as appropriate. Continuous variables will be analyzed using the independent-samples Student’s t-test for approximately normally distributed data or the Mann–Whitney U test for non-normally distributed data.

When a significant group × time interaction is identified, post-hoc pairwise comparisons will be performed to determine differences between groups at each assessment time point and changes within each group over time. The Bonferroni correction will be applied to adjust for multiple comparisons and control the family-wise type I error rate.

The magnitude of the intervention effect will be estimated using mean differences (MD) for continuous outcomes and relative risks (RR) for dichotomous outcomes, with corresponding 95% confidence intervals (95% CI). The number needed to treat for benefit (NNTB) will be calculated for dichotomous outcomes when applicable.

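### The stated 80.75% power belongs to a single unadjusted t-test; the planned analysis is an interaction test followed by Bonferroni-corrected comparisons, and its power is not stated.

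*Protocol article*

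**What the plan says.** **Sample size calculation.** The calculation uses a two-tailed independent-samples t-test, "for the comparison of means between two independent groups", at 5%. It has no term for repeated measures, within-woman correlation or multiplicity. With d = 0.784 it arrives at 27 per arm, "achieving an actual statistical power of 80.75"%, and inflates this to 34 per arm for 20% dropout.

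**Statistical analysis.** The longitudinal outcomes go into a linear mixed model with group, time and group × time, where T0 is one of the levels of time. The interaction is declared the primary parameter. If it is significant, "post-hoc pairwise comparisons will be performed to determine differences between groups at each assessment time point and changes within each group over time", with Bonferroni correction for family-wise error. The size of the Bonferroni family is not given. Baseline values enter the model when judged appropriate.

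**Objective and outcomes.** The Introduction gives the aim as "reducing perineal pain during the postpartum period (change from baseline"), without a time point. Table 3 schedules both pain measures, the NRS and pressure algometry, at T0, T1 and T2.

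**The concern.** The test that was sized is not the test that will decide the trial. A reader of the sample size section would think the trial has 80.75% power for its main conclusion, but no figure is given for the interaction or for the comparisons that follow it.

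Three features make this more than a matter of labels:

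- A significant interaction on 2 degrees of freedom does not say which arm did better or when. The plan leaves that to the comparisons after it, and those are the ones that carry the Bonferroni penalty.
- Some of those comparisons cannot show efficacy. At T0 randomization makes the null hypothesis true. A change within one arm is not a randomized comparison, and entry at NRS 3 or more with analgesics permitted makes improvement in both arms plausible. If these tests share the family, they take alpha from the comparison of interest.
- No pain time point is named as primary. A positive claim could rest on T1 or T2, and on the NRS or algometry.

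**Working it through.** **Inputs.** From the protocol article: two-sided α = 0.05, d = 0.784, 27 evaluable and 34 randomized per arm, and NRS at T0, T1 and T2. Assumed, because the article does not give them: the within-woman correlation ρ (0 to 0.7), compound symmetry, no difference at T0, and equal effects at T1 and T2 unless stated otherwise.

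**1. The plan's own figure.** The noncentrality is d·√(n/2) = 0.784 × √13.5 = 2.881 on 52 df, with critical t = 2.007. Power is 80.7%, which agrees with the stated 80.75% to rounding. For dropout, 54/0.8 = 67.5, rounded up to 68. Both figures reproduce.

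**2. The interaction test.** The group differences in SD units are (0, d, d). Their squared deviations from the mean sum to (2/3)d² = (2/3) × 0.6147 = 0.4098. Then λ = (n/2) × 0.4098/(1 − ρ), which is 5.53/(1 − ρ) for n = 27. The reference is F with 2 and 2(2n − 2) = 104 df.

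| ρ | 27 per arm | 34 per arm |
|---|---|---|
| 0 | 53.5% | 64.3% |
| 0.3 | 69.9% | 80.4% |
| 0.5 | 84.4% | 92.1% |
| 0.7 | 97.4% | 99.3% |

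With 27 per arm, power passes 80.75% near ρ = 0.45. If the T2 effect is half the T1 effect, the sum falls to 0.5d² and power with 27 per arm is 56.5%, 72.1% and 91.7% at ρ = 0.3, 0.5 and 0.7.

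**3. One between-group contrast after Bonferroni, ignoring the interaction requirement.** Three time points give 3 between-group tests. Three pairwise changes in each of two arms give 6 within-group tests, so 9 in all. The formula is that of step 1, with α/3 = 0.0167 or α/9 = 0.0056.

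| d and n per arm | unadjusted | 3 tests | 9 tests |
|---|---|---|---|
| 0.784, 27 | 80.7% | 65.8% | 50.0% |
| 0.784, 34 | 89.0% | 77.9% | 64.3% |
| 0.950, 27 | 92.9% | 84.1% | 72.2% |
| 0.950, 34 | 97.1% | 92.5% | 84.8% |

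The rows at d = 0.950 are there because the article's inputs imply that value. It assumes "4.5 (SD = 3.0) was assumed for the experimental group and 2.0 (SD = 2.2) for the sham group", so the pooled SD is √((3.0² + 2.2²)/2) = 2.631 and d = 2.5/2.631 = 0.950, not 0.784.

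**4. Both steps together.** By simulation at d = 0.784 and 27 per arm, the chance that the interaction is significant and the T1 contrast then passes Bonferroni is 50%, 58% and 64% with 3 tests at ρ = 0.3, 0.5 and 0.7. With 9 tests it is 40%, 45% and 49%.

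**The case against.** The strongest reply is that the interaction is the declared primary test and Bonferroni comes only after it, so the later losses do not bear on primary power. At ρ = 0.5 the interaction has more power than the article claims. This stands, and for that reason a reader who infers that the trial fails to deliver 80.75% goes further than the documents allow. Whether power is lower or higher depends on a correlation and an effect pattern that the article does not give.

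Three further points also stand:

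- The nine-test family is only one reading. The text does not say that between-group and within-group tests share one correction. Separate corrections fit it equally well, and the between-group contrast would then be tested at α/3. The 50.0% is a worst case, and it should not be inferred that the key comparison is tested at 0.0056.
- The 27 per arm allows for 20% dropout, but NRS is last measured 12 h after a single session delivered in hospital. All 34 per arm may be observed, which brings three-test power to 77.9%.
- At d = 0.950, 27 per arm exceeds 80% even over three tests. This is limited comfort. The 80.75% is tied to 0.784, and the stated means give the experimental arm the higher pain score, which is a separate fault to resolve.

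It can also be said that a statistical analysis plan may define the family. But the mismatch between the sized test and the primary test, and the inclusion of every time point and of within-group changes, are in the article's own text. The within-group tests may be meant as description, since efficacy is judged by whether changes differ between groups. If so, they need no place in a Bonferroni family.

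**Conclusion.** The concern holds in this form: the 80.75% was calculated for a test the plan does not use to decide, and the power of the planned analysis is unspecified. At d = 0.784 and 27 per arm, the interaction's power runs from 53.5% to 97.4% as ρ goes from 0 to 0.7, assuming compound symmetry and equal effects at T1 and T2. For a Bonferroni-adjusted contrast it is 65.8% (three tests) or 50.0% (nine, worst case), and 77.9% or 64.3% with all 34 per arm observed. At d = 0.950 and 27 per arm these become 84.1% and 72.2%. The size of any loss is therefore uncertain. Three things do not depend on ρ or d: the sized test differs from the primary test, tests that cannot show efficacy are among the corrected comparisons, and no pain time point is primary.

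**What to change.** Name one primary contrast: the PBM–sham difference in NRS at the one time point the sample-size means refer to. The sponsor should state whether that is T1 or T2 before unblinding. Estimate it from the mixed model and test it at two-sided 5% without requiring a significant interaction. Make the other time point and algometry secondary. Remove T0 and within-group tests from the Bonferroni family and report within-group changes descriptively.

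With that change, 27 evaluable and 34 randomized per arm give about 80.7% power at d = 0.784, so no added enrolment is needed. If the interaction stays primary, restate its power over a stated range of correlations and effect patterns. For comparison, 80% power for a Bonferroni-adjusted contrast at d = 0.784 would need 36 evaluable per arm over three tests (36/0.8 = 45, so 90 women) or 45 over nine (45/0.8 = 56.25, rounded up to 57, so 114 women), against 68 planned.

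The cost is plan wording and a registry update, for which the Protocol amendments section already provides. The small downside is that the time point not chosen becomes secondary.

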Urinary incontinence	International Consultation on Incontinence Questionnaire–Short Form (ICIQ-SF)	Assesses the frequency and amount of urinary leakage and its impact on quality of life.	Total score ranging from 0 to 21.	T3 and T4	Reduction of approximately 2.5–5 points; changes of ≥ 4 points represent a clinically important improvement.
Sexual function	Female Sexual Function Index (FSFI)	Assesses sexual desire, arousal, lubrication, orgasm, satisfaction, and pain during the previous four weeks.	Total score ranging from 2 to 36; cutoff score = 26.55.	T4	Score > 26.55, indicating preserved sexual function.
Adverse events	Standardized clinical record	Assessment of intervention-related adverse events (increased pain, discomfort, skin irritation, hematoma, allergic reaction, or other complications).	Presence/absence; classified according to type and severity.	T1, T2, T3, and T4	Absence of serious treatment-related adverse events.

Legend *T0* pre-intervention, *T1* immediately after the intervention, *T2* 12 hours after the intervention, *T3* 40 days postpartum (late postpartum period), *T4* 3 months postpartum (remote postpartum period)

The baseline assessment will include the collection of sociodemographic and obstetric data, followed by a standardized physical examination. Perineal pain intensity will be assessed using the Numeric Rating Scale (NRS) and pressure algometry. The NRS is an 11-point scale ranging from 0 (no pain) to 10 (the worst pain imaginable), with pain categorized as mild (1–3), moderate (4–6), or severe (7–10). Pain intensity will be assessed using standardized verbal descriptors [18]. 

Pressure pain threshold will be measured using a calibrated MED.DOR^®^ digital pressure algometer, with readings expressed in kgf/cm². The device will be applied perpendicularly to the bilateral peritraumatic region, with one measurement obtained on each side. Participants will be instructed to indicate the moment when the sensation of pressure becomes painful by saying “stop,” and this value will be recorded as the pressure pain threshold. To ensure biosafety, the algometer probe will be covered with disposable plastic film and disinfected with 70% alcohol before each assessment [19].

The use of analgesic medication will be recorded at each assessment point, including the type of medication, dose, route of administration, and time elapsed between medication administration and pain assessment.

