Vulvar Edema Area the area of vulvar edema will be quantified using digital image analysis with ImageJ software (National Institutes of Health, Bethesda, MD, USA). For each photograph, the edematous region will be manually outlined using either the Freehand Selection or Polygon Selection tool according to the anatomical boundaries of the edema. The software will automatically calculate the area of the region of interest (ROI). Images will be calibrated using a reference scale positioned in the same plane as the photographed area, allowing measurements to be expressed in square millimeters (mm²).

Participant satisfaction with the intervention will be assessed using a Visual Analog Scale (VAS) for satisfaction, ranging from 0 (no satisfaction) to 10 (maximum perceived satisfaction), administered at the final assessment [20]. 

Global perceived change will be assessed using the Global Perceived Effect Scale (GPE), which consists of seven response categories ranging from 1 (no change) to 7 (very much better). This outcome will be assessed immediately after the intervention and again 12 h later [21]. 

Immediate postpartum functioning will be evaluated using a 5-point Likert scale, assessing the level of difficulty in performing activities such as standing up, sitting down, walking, and caring for the newborn.

During the late and remote postpartum follow-up assessments, functioning will be evaluated using the World Health Organization Disability Assessment Schedule 2.0 (WHODAS 2.0), which assesses six domains: cognition, mobility, self-care, getting along with others, life activities, and participation. Responses are scored on a 5-point scale ranging from 1 (no difficulty) to 5 (extreme difficulty) [22]. 

Urinary incontinence will be investigated based on participants’ self-reported symptoms and the International Consultation on Incontinence Questionnaire–Short Form (ICIQ-SF), a validated instrument that evaluates the frequency, severity, and impact of urinary leakage on quality of life. Total scores range from 0 to 21, with higher scores indicating greater symptom severity and impact.

Sexual function will be assessed at 3 months postpartum using the Female Sexual Function Index (FSFI), which comprises 19 items distributed across the domains of desire, arousal, lubrication, orgasm, satisfaction, and pain. Total scores range from 2 to 36, with a cutoff score of ≤ 26.55 indicating possible female sexual dysfunction.

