### Participant retention and follow-up

Strategies to maximize participant retention will include clear communication regarding the importance of follow-up assessments, flexible scheduling of follow-up visits, and reminder contacts by telephone or text message.

Participants who fail to attend follow-up assessments will be documented, and the reasons for withdrawal will be recorded whenever possible. All randomized participants will be included in the analyses according to the intention-to-treat principle.

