All primary analyses will follow the intention-to-treat principle. For longitudinal outcomes analyzed using linear mixed-effects models, missing outcome data will be handled using all available observations under the assumption that data are missing at random (MAR), without imputing individual missing time points in the primary analysis. The pattern and reasons for missing data will be described and compared between treatment groups. If the proportion of missing data is substantial, a sensitivity analysis using multiple imputation will be performed to assess the robustness of the results under different assumptions regarding missing data.

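### WHODAS 2.0, ICIQ-SF and FSFI have no in-hospital values, so women with no late assessment cannot be in those analyses, contrary to the statement that all randomized participants are included

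*Protocol article*

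**What the plan says.** **Analysis population.** The section Participant retention and follow-up, directly after describing women who miss follow-up visits, states: "All randomized participants will be included in the analyses according to the intention-to-treat principle". The Adverse events section repeats this for women who withdraw because of an adverse event. The Statistical analysis section is narrower: "All primary analyses will follow the intention-to-treat principle".

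**Missing data.** For longitudinal outcomes in the mixed models, the Statistical analysis section states: "missing outcome data will be handled using all available observations under the assumption that data are missing at random (MAR"). Individual missing time points are not imputed in the primary analysis. Multiple imputation is a sensitivity analysis, to be run if a substantial proportion of data is missing. The article gives no threshold.

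**Model.** The fixed effects are group, time and their interaction, and participant is a random effect. The only covariate mentioned is the outcome's own baseline value, where appropriate.

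**Timing of the late outcomes.** For WHODAS 2.0: "During the late and remote postpartum follow-up assessments, functioning will be evaluated using the World Health Organization Disability Assessment Schedule 2.0". Table 3 gives T3 and T4 for WHODAS 2.0 and for ICIQ-SF. For FSFI: "Sexual function will be assessed at 3 months postpartum using the Female Sexual Function Index (FSFI"), which is T4 only. None of the three has a value at T0, T1 or T2.

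**Dropout.** The sample size section reads "Considering an anticipated dropout rate of 20" per cent, which raises 54 women to 68.

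**The concern.** An available-data mixed model supports an all-randomized analysis when each woman has at least one early value. That is the case for the pain scale, which is measured at T0, T1 and T2. The model then keeps a woman with missing later scores and conditions on the scores she did give.

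The late outcomes have no such early value. A woman not reached at 40 days or 3 months has no record in the WHODAS 2.0 or ICIQ-SF model, and one not reached at 3 months has no FSFI score. The comparison becomes one among women who returned.

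The MAR assumption also asks more here. With no early value and no other covariate, the only thing the model knows about a woman never seen after discharge is her arm. If return depends on early pain or early recovery, and these also predict late functioning, incontinence or sexual function, the comparison can be biased. The trial collects pain and functioning scores at T0, T1 and T2, but the article gives them no role in these models.

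**Working it through.** **1. The plan's own figure.** 54 / (1 − 0.20) = 67.5, rounded up to 68, or 34 per arm. This matches the article.

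**2. Women absent from the late analyses.** The article does not say when dropout occurs, and its 20% was set for a pain comparison. Taking it as loss before T3 is therefore an assumption.

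| Assumed loss before T3 | Women absent | Women analysed (WHODAS, ICIQ-SF) |
|---|---|---|
| 10% | 68 × 0.10 = 6.8, about 7 | 61 |
| 20% (plan's dropout rate) | 68 × 0.20 = 13.6, about 14 | 54 |
| 30% | 68 × 0.30 = 20.4, about 20 | 48 |

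**3. Women lost between T3 and T4.** Suppose 14 women are lost before T3 and a further 5 (an illustrative number) between T3 and T4. A group × time mixed model with T3 and T4 records then holds 54 women and 54 × 2 − 5 = 103 records. The 5 women stay in through their T3 values. An analysis at T4 only, as for FSFI, holds 54 − 5 = 49 women.

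**4. What MAR requires, outcome by outcome.**
- Pain (T0–T2): loss may depend on arm and on the woman's earlier pain scores.
- WHODAS 2.0 and ICIQ-SF, seen at T3 but not T4: loss may depend on arm and on the T3 value.
- WHODAS 2.0 and ICIQ-SF, seen at neither: loss may depend on arm only.
- FSFI: the missing-data rule covers longitudinal mixed-model outcomes, so it does not reach a single measurement. An analysis of the women with a score again requires loss to depend on arm only.

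**5. How large could the bias be?** The article cannot answer this, so the following is illustration only. Assumptions: 20% loss overall; no true effect on the late outcome; PBM lowers T2 pain by 0.8 SD; T2 pain correlates 0.3 to 0.7 with the late outcome; where loss depends on pain, the log-odds change by 1 per SD. Bias is in SD of the late outcome.

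| Loss before T3 | Bias without early data | After conditioning on T2 pain |
|---|---|---|
| Unrelated to pain | about 0 | about 0 |
| Rises with pain in both arms | 0.03 to 0.06 | within 0.012 of 0 |
| Rises with pain in sham only | 0.06 to 0.13 | within 0.012 of 0 |
| Rises with pain in sham, falls with pain in PBM | 0.11 to 0.24 | within 0.012 of 0 |

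For scale, with 27 women per arm the standard error of a difference is √(2/27) = 0.27 SD. The largest value in the table is thus 0.24 / 0.27, a little under one standard error, and most are well below half.

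Two features limit what can be read from this table. Swapping the arms in the last row reverses the sign. In the second row the bias arises because the arms lose different proportions (about 25% sham, 15% PBM); with equal loss in each arm it vanishes.

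**The case against.** The strongest reply is that only secondary outcomes are touched. The intention-to-treat sentence in the Statistical analysis section is confined to primary analyses, the main aim is perineal pain, and pain is measured in hospital. The Discussion already says the late outcomes are not direct evidence of a long-term effect of one session. The plan also commits to retention measures, to comparing reasons for missingness by arm, and to imputation if much is missing. An available-data model first with imputation as sensitivity analysis is a common order, and thresholds are usually left to the analysis plan. All of this stands, and it limits the weight of the point. It does not remove the conflict, because the sentence under Participant retention and follow-up has no restriction to primary analyses and stands where late visits are discussed.

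A reader might infer more than the article supports:
- *That every woman lost after discharge drops out.* Those seen at T3 stay in the WHODAS 2.0 and ICIQ-SF models.
- *That MAR gives no protection at all.* It gives some to those women, and the analysis is valid if loss depends only on arm.
- *That the article applies its mixed-model rule to FSFI.* The rule's stated scope excludes a single-timepoint outcome. A separate FSFI rule may sit in a document not shown, and its absence here is not counted as an error.
- *That the late effect will be diluted by a known percentage.* The correlations and loss patterns needed for that have no source in the article, and the sign can reverse.
- *That multiple imputation must become the main analysis.* With about 27 observed women per arm and many candidate auxiliaries, this is a debatable trade-off.

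It is also fair to object that T0 covariates bring back no lost woman and do not deal with loss driven by T2 pain. That is why the imputation step is needed as well.

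**Conclusion.** The point holds for three secondary outcomes. From the measurement schedule and the no-imputation rule alone, a woman with no T3 or T4 value (no T4 value for FSFI) cannot be in these analyses, so the unrestricted all-randomized statement cannot be met. This needs no assumption. The count does: about 14 of 68 women if the planned 20% dropout all falls before T3, fewer if part of it falls later, more if late attrition exceeds 20%.

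The analysis also relies, for women never seen after discharge, on loss being unrelated to the late outcome given arm, although data that could weaken that requirement are collected. Whether bias follows, and in which direction, cannot be known from the article. The primary pain analysis is not affected. This is a correction worth making before analysis, not a threat to the trial's main conclusion.

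**What to change.** 1. **Correct the population statement.** In Participant retention and follow-up, limit the all-randomized sentence to outcomes with in-hospital measurements. State that WHODAS 2.0 and ICIQ-SF are analysed in women with at least one T3 or T4 value, and FSFI in women with a T4 value, each in the allocated arm. Report these numbers by arm.
2. **Use baseline data.** Enter T0 pain (NRS) and T0 functioning as covariates in the WHODAS 2.0, ICIQ-SF and FSFI models. Do not enter T1 or T2 scores there: they follow treatment, and adjusting for them would change the effect being estimated.
3. **Make the planned imputation unconditional for these outcomes.** Run the multiple-imputation sensitivity analysis for all three, however much is missing, with T0–T2 pain and functioning scores as auxiliary variables. The post-treatment scores belong in this step.

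The cost is a few sentences and a modest amount of analysis; every variable is already collected. The downside is that an imputation model must be specified in advance and kept small, since only about 27 women per arm (34 × 0.80 = 27.2) would have observed late values under the 20% assumption.
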